#### **6.4 Expedited Adverse Event (EAE) Reporting to DAIDS**

The expedited adverse event (EAE) reporting requirements and definitions for this study and the methods for expedited reporting of adverse events (AEs) to the DAIDS Regulatory Compliance Center (RCC) Safety Office are defined in “The Manual for Expedited Reporting of Adverse Events to DAIDS” (DAIDS EAE Manual), **dated May 6, 2004**. The DAIDS EAE Manual is available on the RCC website: <http://rcc.tech-res-intl.com/>.

AEs reported on an expedited basis must be documented on the DAIDS Expedited Adverse Event Reporting Form (EAE Reporting Form) available on the RCC website: <http://rcc.tech-res-intl.com/>.

**“Expedited adverse event”** (EAE) means:

An adverse experience that meets the criteria for expedited reporting to DAIDS.

**“Serious adverse drug experience”** (SAE) means:

Any adverse drug experience occurring at any dose that results in any of the following outcomes-

- ⊙ Death (All reported as EAEs)
- ⊙ a life-threatening adverse drug experience (Only SADR reported as EAEs)
- ⊙ inpatient hospitalization or prolongation of existing hospitalization (Only SADR reported as EAEs)
- ⊙ persistent or significant disability/incapacity
- ⊙ congenital anomaly/birth defect (All reported as EAEs, including unintentional fetal loss, per DAIDS)

Important medical events that may not result in death, be life-threatening, or require hospitalization may be considered a serious adverse drug experience if the event is determined to be serious based upon appropriate medical judgment, may jeopardize the subject and/or requires medical or surgical intervention to prevent one of the outcomes listed in this definition.

##### **6.4.1 EAE Reporting Requirements for this Study**

###### EAE Reporting Level

This protocol will use the DAIDS Standard Level of reporting as defined in the DAIDS EAE Manual.

### Study Agents for Expedited Reporting to DAIDS

The study agent that must be considered in determining relationships of AEs requiring expedited reporting to DAIDS are UC-781 gel/placebo and the study agent delivery applicators.

### Grading Severity of Events

The DAIDS Table for Grading the Severity of Adult and Pediatric Adverse Events (DAIDS AE Grading Table), Version 1.0, December, 2004, must be used and is available on the RCC website at <http://rcc.tech-res-intl.com/>. In addition to the DAIDS AE Grading Table, there are protocol-specific adverse event grading criteria, which can be found in Section 6.2 and Appendix IV of this protocol.

### EAE Reporting Period

AEs must be reported on an expedited basis at the Standard Level during the Protocol-defined EAE Reporting Period, which is:

- The entire study duration for an individual subject (from enrollment until study completion or discontinuation of the subject from study participation for any reason).

After the end of the Protocol-defined EAE Reporting Period stated above, sites must report serious, unexpected, clinical suspected adverse drug reactions if the study site staff becomes aware of the event on a passive basis, i.e., from publicly available information.

### **6.4.2 Timetable for Reporting**

Any adverse events that are serious (whether expected or unexpected) and possibly associated with use of the drug must be immediately reported to CONRAD and DAIDS by telephone (21 CFR 312.64). If there is any question whether the adverse event meets any criteria of severity, it should be reported by telephone to the CONRAD and DAIDS. In addition, a completed Expedited Adverse Event (EAE) Form must be faxed to the RCC Safety Office within 3 business days (by 5 PM EST) after site awareness that the event has occurred at a reportable level and to CONRAD as soon as possible.

CONRAD will notify the FDA by telephone or fax of any unexpected serious adverse events associated with the use of the drug as soon as possible, but no later than 7 calendar days after initial receipt of the information from the investigator. In addition, CONRAD will inform the FDA in writing. The written notification will be made as soon as possible and in no event later than 15 calendar days after initial receipt of the information.

DAIDS and CONRAD will follow all serious adverse events with the cooperation of the investigator.

All serious adverse events will be reported promptly to the Institutional Review Board by the investigator.

Events that are not serious, but are associated with treatment and unexpected must be reported to the Institutional Review Board by the investigator according to local IRB requirements.

## **7.0 STATISTICAL CONSIDERATIONS**

### **7.1 Review of Study Design**

A total of 36 participants randomized to one of 3 treatment arms, each undergoing 2 treatment phases. All subjects will progress through the both phases. In the first treatment phase, subjects will receive a single dose of study product administered rectally in the clinic. In the second treatment phase the subject will self-administer once daily rectally administered outpatient doses for 7 days. After each treatment phase subjects will undergo clinical evaluation and specimen collection.

### **7.2 Randomization of Treatment Assignments**

The randomization codes will be generated by the UCLA MDP Biostatistics Core, using computer-generated random numbers. Randomization will be performed in blocks of six, with each block containing two assignment codes for each of the three treatment groups. These randomization codes can be thus represented as randomly permuted strings of six letters: two A's, two B's, and two C's. Randomization blocks will be generated sequentially allowing for correction of any imbalance due to the withdrawal of a participant prior to receiving any doses of the study agent.

In addition, to randomize subjects for the pK substudy, beginning with the first block of six letters, one "A", one "B", and one "C" will be randomly tagged with a "pK" to denote the subject has been selected for the substudy. Should all subjects consent, the substudy randomization will thus be completed after the first three blocks of 6 subjects. If any subjects refuse substudy participation, this subrandomization will continue as needed until three subjects from each treatment arm have been recruited for the substudy.

Once generated the UCLA investigational pharmacy with primary responsibility for drug dispensing will be responsible for randomizing subjects and maintaining the blind.

### **7.3 Unblinding**

Once the data set has been locked down per the SSP Manual, the investigators may break the blind. See Section 6.1 for unblinding of the SMC in the case of a non-emergent safety review.

#### **7.3.1 Emergency Unblinding Procedures**

Subjects may be unblinded for safety or medical treatment purposes. The investigator must, whenever possible, phone the study's designated SMC medical monitor to unblind the code. The medical monitor will notify the investigator and sponsor that a subject was unblinded without revealing what the treatment assignment was. Appropriate documentation must be submitted to the investigator and CONRAD within 3 working days of unblinding. Any subject that is unblinded must be discontinued from the study.

The Emergency Unblinding Code specifying the subject's treatment code is located on the drug label. Only in case of medical emergency, can the investigator break the masking code by scratching off the unmasking cover. This label is affixed to the drug label source.

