### 6.3 Adverse Experience Reporting Requirements

Study participants will be provided with a list of danger signs and a 24-hour telephone number. Participants will be instructed to contact the study clinician to report not only danger signs, but also any events they may experience, except for life-threatening events, for which they will be instructed to seek immediate emergency care. Depending on the severity of the event, the clinician will instruct the participant to present to the study site (for more mild events) or to an emergency room (for more serious events) for immediate evaluation. Where feasible and medically appropriate, participants will be encouraged to seek medical care where the study clinician is based, and to request that the clinician be paged or otherwise contacted upon their arrival. With appropriate permission of the participant, records from all non-study medical providers related to such events will be obtained and required data elements will be filed with the source documentation. All participants reporting an AE will be followed clinically, until the AE resolves (returns to baseline), stabilizes or their last study visit. Subjects may be followed for longer periods of time per the discretion of the investigator, DAIDS, and the sponsor.

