## **7.10 Statistical Procedures for Missing Data**

All reasonable efforts will be made to obtain complete data for all patients; however, missing observations will occur due to missed visits, patients lost to follow-up, or noncompliance with the full acceptability assessment or secondary measures. In order to account for this, and to be able to perform intent to treat analysis on the outcomes, multiple imputation will be employed. The imputation will be implemented using the MI procedure in SAS or the IveWARE library. In order to construct these models independently of the data from the current study, imputation model building will be based wherever possible on the data from HPTN 056.

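### Emergency unblinding ends study participation, not only product use, so later adverse events and scheduled outcomes of that participant are avoidably lost

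*Protocol*

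**What the plan says.** Protocol Section 7.3.1 gives the grounds for breaking an individual code: "Subjects may be unblinded for safety or medical treatment purposes". The consequence follows without exception: "Any subject that is unblinded must be discontinued from the study". The rule concerns the study as a whole; the section has no separate provision for product use and for follow-up.

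Five other places decide what that consequence means in practice.

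- **Section 6.4.1, EAE Reporting Period.** Active expedited reporting runs "from enrollment until study completion or discontinuation of the subject from study participation for any reason". After that, "sites must report serious, unexpected, clinical suspected adverse drug reactions if the study site staff becomes aware of the event on a passive basis".
- **Section 6.3.** On ordinary adverse events: "All participants reporting an AE will be followed clinically, until the AE resolves (returns to baseline), stabilizes or their last study visit". Longer follow-up is allowed at the discretion of the investigator, DAIDS and the sponsor.
- **Section 6.4.2.** DAIDS and CONRAD follow all serious adverse events with the investigator's cooperation. No end point is given.
- **Section 3.5.** Those who leave early are offered a final evaluation on a best-effort basis. Those withdrawn after receiving product are not replaced.
- **Section 7.10.** Multiple imputation is planned "to be able to perform intent to treat analysis on the outcomes". The foreseen causes of missing data are missed visits, loss to follow-up and noncompliance.

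**The concern.** Unblinding is done here for safety or medical reasons. A rule that turns it into departure from the study stops routine observation of a participant because of a safety or medical concern. Section 8.3 says that this formulation has not been tested rectally in humans and that its risks are not known, so what happens to such a participant afterwards is part of what the trial is meant to learn.

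Two things are at stake. The first is surveillance: new events after the departure no longer fall under active expedited reporting. The second is the analysis. Data that stop because of a safety concern are probably not missing at random, and Section 7.10 does not foresee missingness that the protocol itself imposes. It builds the imputation models, where possible, on HPTN 056, which Section 1.1 describes as characterising baseline mucosal indices in men. As described, that source says little about the course of a person unblinded after using the gel.

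**Working it through.** The point is textual, so the sections are read together first. A small calculation then gives the scale.

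**1. What ends at discontinuation.** Section 7.3.1 ends study participation. Section 6.4.1 ends the expedited reporting period at that same moment, whatever the reason. The scheduled contacts still ahead (the follow-up calls, Visits 4 and 5, the interview) have no stated basis for continuing. By the nominal schedule, a participant unblinded at Visit 3 (Week 2) has 6 − 2 = 4 weeks left to Visit 5 (Week 6); both visits have windows.

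**2. What does not end.** The prompting event happens while the participant is enrolled, so it is inside the reporting period and is recorded. Section 6.4.2 keeps serious events under follow-up. Section 6.4.1 keeps passive reporting of serious, unexpected suspected reactions. Section 3.5 seeks a final evaluation.

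**3. What is left uncovered.**

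| Later information | Status after unblinding |
|---|---|
| Course of the prompting event, if serious | Followed (6.4.2) |
| Course of the prompting event, if not serious | Required only to resolution, stabilisation or last visit; longer is discretionary (6.3) |
| New serious, unexpected suspected reaction | Reportable if learned of passively (6.4.1) |
| Other new events | No stated duty of active ascertainment beyond the final evaluation |
| Remaining scheduled outcomes | Not collected, except what the final evaluation yields |

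Section 6.4.2 gives no end date for reporting serious, possibly associated events, while Section 6.4.1 does. The documents do not say which governs a new serious event after discontinuation.

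**4. The protocol separates these ideas elsewhere.** Under the pregnancy provision in Section 6.3 a participant is withdrawn, yet every reasonable effort is made to follow her to outcome. Section 5.7.2 carries out Visit 5 for safety even when an STI result is positive. Section 7.3.1 has no comparable provision.

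**5. Scale.** One participant is 1/12 = 8.3% of an arm. The only figures in Section 7.4 are probabilities of seeing at least one event in a group of 12, that is 1 − (1 − p)^n:

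- p = 0.20, n = 12: 1 − 0.80^12 = 0.931 (protocol: more than 90%)
- p = 0.01, n = 12: 1 − 0.99^12 = 0.114 (protocol: 11%)

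Both reproduce. If 1, 2 or 3 participants contributed no observation at all:

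| n observed | p = 0.20 | p = 0.01 |
|---|---|---|
| 12 | 93.1% | 11.4% |
| 11 | 91.4% | 10.5% |
| 10 | 89.3% | 9.6% |
| 9 | 86.6% | 8.6% |

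The losses of 1, 2 and 3 are assumptions, since the documents do not say how many unblindings to expect. For each assumed number the table overstates the loss, because an unblinded participant has been observed up to that point and an event that led to unblinding already counts.

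**The case against.** The case against is strong on scope, and most of it stands.

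- **A reader might infer that expedited reporting ends altogether for the participants with the most serious events.** It does not. The prompting event remains reportable, serious events are followed under Section 6.4.2, and a passive route stays open. That these participants have the most serious events is also an inference; the protocol says only that unblinding is for safety or medical treatment.
- **A reader might infer a contradiction with intent to treat.** Section 7.3.1 takes a participant out of the study, not out of the analysis, and Section 7.10 plans imputation so that everyone can be analysed. The rule creates avoidable missing data, which weakens the principle without negating it.
- **A reader might infer that the primary endpoint is biased in favour of a harmful arm.** This is not shown. If an event of Grade 2 or higher prompts the unblinding, it is already counted in the assigned arm. Counted per participant, nothing is lost; counted per event, only later events can be missed. A direction of bias would also require unblinding to be more frequent in one arm.
- **A reader might infer that an early unblinding forfeits a whole Stage 2 record.** Stage 2 requires its own clearance (Sections 5.5 and 5.6), the stages are declared independent, and Visit 5 is tied to Day 8 of Stage 2. Someone who would not have taken Stage 2 product has no Stage 2 exposure outcome to lose.

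What the objection does not remove is the gap for new, later events. The Section 3.5 evaluation is a single best-effort contact, longer follow-up under Section 6.3 is discretionary, and neither reopens the period that Section 6.4.1 closes. A statistical analysis plan cannot recover data that the protocol has stopped collecting.

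**Conclusion.** The concern holds in a limited form. Applied as written, Section 7.3.1 together with Section 6.4.1 ends active expedited reporting of new events and removes the remaining scheduled safety contacts for a participant unblinded for safety or medical treatment. The loss is confined to later adverse events and scheduled outcomes. It is avoidable and probably informative, and it undermines the intent-to-treat aim.

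The size is 8.3% of an arm per participant, without replacement after dosing. The number affected cannot be derived from the documents and may be zero. The conclusion assumes that discontinuation from the study means what Section 6.4.1 takes it to mean; no provision in the protocol gives it a narrower sense. The change is worth making because it is cheap, not because a large distortion has been demonstrated.

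**What to change.** Amend Section 7.3.1 so that unblinding does not by itself end study participation. The participant should:

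- stay in adverse event follow-up and in the expedited reporting period to the scheduled end of study;
- be flagged as unblinded in the data;
- be analysed in the assigned arm.

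Reconcile Sections 3.5, 6.3, 6.4.1 and 6.4.2 with this. State which of 6.4.1 and 6.4.2 governs a new serious event, and what the scheduled end is for someone who never starts Stage 2, since Visit 5 is defined from Stage 2 dosing. Leave decisions on product use and on invasive procedures, including the Visit 5 sigmoidoscopy and biopsies, to the sponsor's existing clinical provisions.

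The cost is a sentence or two in Section 7.3.1 and matching edits in the related sections. The drawback is a few observations on subjective items made without the blind; the flag identifies them and allows a sensitivity analysis.

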### **7.4 Statistical Procedures for Analysis of Safety Data**

The frequency of  $\geq$  Grade 2 adverse events will be used as the primary measure of safety of UC-781. Because of the relatively small sample size, only large differences between placebo and study drug groups will be detectable. As an example, there is more than a

90% probability that one or more adverse events will be seen in a group of 12 subjects when the true rate of events is 20%. In contrast, when the true event rate is only 1%, there is an 11% chance of observing one or more AE's in a group of 12 subjects. When the adverse event represents an exacerbation of a baseline condition, the adverse event will be reported as the change in grade from baseline. Serious adverse events will be reported as such, regardless of the baseline condition.

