### **3.2 Exclusion Criteria**

Individuals who meet any of the following criteria at screening will be excluded from the study:

1. HIV positive at baseline
2. History of inflammatory bowel disease
3. Active inflammatory condition of the GI tract at baseline
4. Active rectal infection at baseline
5.  $\geq$  Grade 2 laboratory abnormality at baseline
6. History of an underlying cardiac arrhythmia or renal disease that may be exacerbated by electrolyte abnormalities.
7. History of severe or recent cardiac or pulmonary event
8. History of a large aortic aneurysm
9. History of significant gastrointestinal bleeding
10. Allergy to methylparaben, propylparaben, sorbic acid
11. History of alcoholism or IV drug abuse
12. Unwillingness to refrain from chronic use of aspirin and NSAIDs.
13. Use of warfarin or heparin
14. Use of systemic immunomodulatory medications within 4 weeks of Visit 2
15. Use of rectally administered medications, with the exception of over-the-counter enemas, within 4 weeks of Visit 2
16. Use of product containing nonoxyl-9 rectally within 4 weeks of Visit 2

17. Use of any investigational products within 4 weeks of Visit 2
18. Any other clinical condition or prior therapy that, in the opinion of the investigator, would make the patient unsuitable for the study or unable to comply with the study requirements. Such conditions may include, but are not limited to, current or recent history of severe, progressive, or uncontrolled renal, hepatic, hematological, gastrointestinal, endocrine, pulmonary, neurological, or cerebral disease.

**In addition to the criteria listed above, female participants will be excluded if they meet any of the following criteria:**

19. Pregnancy
20. Breastfeeding
21. Female of child-bearing potential unwilling to use acceptable form of contraception

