## 6.0 SAFETY MONITORING AND ADVERSE EVENT REPORTING

### 6.1 Safety Monitoring

The study site Investigators are responsible for continuous close safety monitoring of all study participants, and for alerting the protocol team if unexpected concerns arise. The protocol team will meet via conference call every two to four weeks during the period of study implementation, and additional ad hoc calls will be convened, if required. A decision to convene the SMC may be made at any time that the team agrees that an unacceptable type and/or frequency of AEs has been observed.

In addition, accrual will be suspended and the UCLA SMC will be convened, if **two or more** study participants experience an **AE  $\geq$  Grade 3**. If the SMC feels the AE's may be sufficient to halt the trial, the SMC will be unblinded. The SMC will then analyze the data in an unblinded fashion and make the determination on whether to continue accrual and product use. No other study staff will be unblinded until the study has been terminated and the data locked down.

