### 6.2 Adverse Event Evaluation Criteria

An AE is defined as any untoward medical occurrence in a clinical research participant administered an investigational product and which does not necessarily have a causal relationship with the investigational product.

All gastrointestinal AEs will be defined and graded as described in the 2006 DAIDS Rectal Toxicity Table Addendum (Appendix IV). Any AEs not defined in the DAIDS Rectal Toxicity Table will be defined and graded as described in the DAIDS Toxicity Table (Appendix V). The DAIDS Toxicity Table can be found in Appendix V and on-line at <http://rcc.tech-res-intl.com/>.

Each adverse event not described above or in the DAIDS Toxicity Table should be graded for severity using the following scale:

- ⊙ Mild: subject was aware of the adverse event, but she/he was still able to do all activities; no or minimal medical intervention/therapy required.
- ⊙ Moderate: the subject had to discontinue some activities due to the adverse event; no or minimal medical intervention/therapy required.
- ⊙ Severe: the subject was incapacitated by the adverse event and unable to perform normal activities; significant medical intervention/therapy required, hospitalization possible.

For pre-existing lab abnormalities and conditions, only changes  $\geq$  one Grade level will be reported as adverse events.

It is the responsibility of the investigator to determine if an adverse event is definitely related, possible related, probably related or, unrelated to the subject's participation the

study. The investigator or designee will assess the relationship of all AEs to the study product based on the DAIDS EAE Reporting Manual, the Investigator's Brochure, and his/her clinical judgment.

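### Section 7.4 reports a worsened baseline condition as its change in grade; read literally, a non-serious Grade 1-to-2 worsening misses the primary endpoint of Grade 2 or higher adverse events

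*Protocol*

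**What the plan says.** Section 7.4 of the protocol sets the primary safety measure as a frequency with a threshold: events at or above "Grade 2 adverse events will be used as the primary measure of safety of UC-781".

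Later in the same paragraph it gives a rule for participants who already had the condition: "When the adverse event represents an exacerbation of a baseline condition, the adverse event will be reported as the change in grade from baseline". The next sentence makes one exception: "Serious adverse events will be reported as such, regardless of the baseline condition".

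Other sections bear on the grade of such an event:

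- Section 6.2 sets the scale: "All gastrointestinal AEs will be defined and graded as described in the 2006 DAIDS Rectal Toxicity Table Addendum". Events outside that table go to the general DAIDS table. For pre-existing laboratory abnormalities and conditions, a change of at least "one Grade level will be reported as adverse events".
- Section 6.4.1 makes the DAIDS grading table mandatory, in the context of expedited reporting.
- Section 3.2, exclusion 5, bars anyone at or above "Grade 2 laboratory abnormality at baseline". A Grade 1 laboratory abnormality is therefore compatible with entry.
- Sections 5.3.1 and 5.6 hold a participant back from the next treatment stage when a laboratory abnormality is Grade 2 or higher, without reference to the baseline grade.

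**The concern.** The primary measure is a threshold on grade, and the rule for exacerbations replaces the grade with a difference of grades. These are different scales. A change of 1 can mean that Grade 1, 2, 3 or 4 was reached, depending on where the participant started. If the change is what is compared with the threshold of 2, a non-serious event that the DAIDS tables call Grade 2 goes uncounted.

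At stake is the main safety result of a study with 12 participants per arm, in which Section 7.4 itself warns that only large differences will be detectable. One or two events moved in or out of the count would matter to the reading of an arm. Because a change in grade can never exceed the grade reached, any error runs one way, towards fewer counted events. The protocol would also treat the same result in two ways: a laboratory value rising from Grade 1 to Grade 2 at Visit 3 triggers the hold in Section 5.6, yet under the literal wording of Section 7.4 it does not count towards the primary endpoint.

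**Working it through.** **1. The plan's own figures.** Section 7.4 gives, as an example, a value above the following: "90% probability that one or more adverse events will be seen in a group of 12 subjects when the true rate of events is 20" per cent. It also gives an 11% chance for a true rate of 1%. With n = 12 and P(at least one) = 1 − (1 − p)^12:

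- p = 0.20: 1 − 0.80^12 = 0.931
- p = 0.01: 1 − 0.99^12 = 0.114

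Both stated figures reproduce and are not in question.

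**2. Which worsenings are affected.** Let b be the baseline grade and w the worst grade reached. Compare w ≥ 2 (grade attained, DAIDS tables) with w − b ≥ 2 (literal Section 7.4), for non-serious events.

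| b to w | Change | Counted by grade attained | Counted by change |
|---|---|---|---|
| 0 to 2 | 2 | yes | yes |
| 0 to 3 | 3 | yes | yes |
| 1 to 2 | 1 | yes | **no** |
| 1 to 3 | 2 | yes | yes |
| 2 to 3 | 1 | yes | **no** |
| 2 to 4 | 2 | yes | yes |
| 3 to 4 | 1 | yes | **no** |

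The two rules agree for every event that starts from Grade 0. They differ for one-grade worsenings from Grade 1 or above. The 1-to-2 row is the one that eligibility clearly leaves open, since exclusion 5 admits Grade 1 laboratory abnormalities. The rows starting at Grade 2 or 3 could apply only to non-laboratory conditions, or to laboratory values that changed after screening.

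**3. Does another section settle it?** Section 6.2 decides when a worsening becomes an adverse event (one grade or more) and on which scale events are graded. It does not say which number enters the Grade 2 or higher count for an exacerbation. Section 6.4.1 names the table and is also silent on this. Neither subtracts a baseline grade. No section overrides the sentence in Section 7.4.

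**4. Illustration of size.** The protocol does not give the share s of Grade 2 or higher events that are one-grade worsenings, so s is an assumption. Take the plan's 20% as the true probability that a participant has a qualifying event, and suppose that a participant whose event is lost has no other. The counted rate is then 0.20 × (1 − s):

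| s (assumed) | Counted rate | P(at least one in 12) |
|---|---|---|
| 0% | 20% | 93.1% |
| 10% | 18% | 1 − 0.82^12 = 90.8% |
| 25% | 15% | 1 − 0.85^12 = 85.8% |
| 50% | 10% | 1 − 0.90^12 = 71.8% |

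**The case against.** The strongest reply is that Section 7.4 says how an exacerbation is reported. It does not expressly say that the change is the number compared with the Grade 2 threshold. On a softer reading the shift is displayed and the grade reached is counted. Sections 6.2 and 6.4.1 support that reading, and the sentence on serious events is also about reporting. Section 6.3 has every adverse event documented whatever its severity, so the data would survive and either count could be derived later.

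Much of this stands. It is not established that these events will be dropped; that follows only from the literal wording. But the softer reading is written nowhere, and two analysts could obtain different primary counts from the same data. Nor is this a detail left for an analysis plan, because the protocol itself states the rule, next to the endpoint with which it conflicts.

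It is also fair to say that the number of affected events may be small. Section 1.3 describes healthy volunteers, and Section 3.2 excludes inflammatory bowel disease, active gastrointestinal inflammation, active rectal infection and laboratory abnormalities of Grade 2 or higher. At an assumed share of 10% the probability is 90.8%, still above the plan's 90%.

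Two stronger inferences are tempting and lack support:

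- A reader might conclude that a participant with a Grade 1 baseline must reach Grade 4 before the Section 6.1 trigger applies, under which "accrual will be suspended and the UCLA SMC will be convened". Nothing carries the Section 7.4 wording over to Section 6.1. That trigger refers to an event of Grade 3 or higher, and grading for that purpose belongs to Section 6.
- A reader might suppose that the lost events are the ones an irritant gel would most likely cause. The protocol gives no basis for this. Irritation arising from Grade 0 counts the same under both rules.

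**Conclusion.** The point holds as a conflict in how the primary safety endpoint is counted. Under the literal wording of Section 7.4, a non-serious Grade 1-to-2 worsening is reported as 1 and falls below the threshold, against the DAIDS grading in Sections 6.2 and 6.4.1. Under the softer reading the count is right, but the protocol does not say so.

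The direction is certain if the literal rule is applied: the count can fall and cannot rise. The size is unknown. The figures of 90.8%, 85.8% and 71.8% against 93.1% show sensitivity to assumed shares of 10%, 25% and 50%; they are not estimates for this trial. They also rest on treating 20% as a per-participant probability and on no affected participant having a second qualifying event. The illustrative probabilities printed in Section 7.4 are correct for the rates they name. The conclusion does not extend to the safety committee trigger or to any claim about which kind of event is lost.

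**What to change.** Replace the sentence on exacerbations in Section 7.4 with wording such as: a worsening of a baseline condition by at least one grade is an adverse event and is counted in the primary endpoint at the DAIDS grade attained; the baseline grade is shown alongside in a shift table. Then align the sentence on pre-existing conditions in Section 6.2, so that both sections use the same rule for when a worsening is an event and at what grade it is counted.

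The cost is one or two sentences and one additional table. No new data are needed, because Section 6.3 already has all adverse events recorded regardless of severity. The counted frequency may be somewhat higher than under the literal rule. The shift table keeps the information on worsening from baseline that the present sentence seems meant to convey.
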